## **1.2 - EXPECTED RESULTS AND PROSPECTS**

The study will be conducted in patients between the ages of 50 and 85 years with knee osteoarthritis for which total knee arthroplasty has been scheduled by the surgeon. Two patient groups will be studied: one of the two groups will undergo four group sessions including therapeutic education and physical exercises, a knee arthroplasty guide and an exercise CD at least 2 months before the intervention; the other group (control group) will receive the usual information and advice given by the surgeon and according to each centre, and a knee arthroplasty guide.

If this programme is confirmed to be effective, it should lead to a reduction in the length of hospital stay and rate of transfers to rehabilitation care facilities, achieving quicker and more complete functional recovery, improving the patient's quality of life and satisfaction, and reducing treatment costs.

## **1.3 - STUDY FEASIBILITY**

The feasibility of the study is attested by:

- The experience of the clinical teams in the pre- and postoperative management and treatment (particularly treatments including education and physiotherapy) of TKA, with the institutional recognition of the orthopaedic centres ensuring sufficient recruitment;
- Standardisation of the intervention;
- The existence of a cross-functional, complementary steering committee: methodological, logistical and clinical, with an adviser per department, including the principal investigator.

## **1.4 - EXPECTED BENEFITS AND RISKS**

Carrying out a multidisciplinary programme combining education and exercises should lead to quicker and more complete functional recovery, reduce the length of hospital stay and the rates of transfers to rehabilitation care facilities, improving the patient's quality of life and satisfaction, and reducing treatment costs.

The risks are minimal, and are related to the adverse events which may occur during the study.

We have no known or reported factors regarding the risks related to the education programme. The main risks related to the exercise programme are the increase in exercise-related pain and exercise-related injuries to muscles (cramps, elongation), ligaments (sprain) and joints (effusion). If any events occur, the patients will be assessed by the doctor in charge of the study for their treatment. These are minor, non-progressive injuries which are quick to heal, as the exercise intensity will be adapted to the patient's pathology and age, under the supervision of a physiotherapist.

## **II - STUDY OBJECTIVE**

### **II.1 - PRIMARY OBJECTIVE**

The primary objective of this study is to assess the effectiveness of the programme on:

- ability, at discharge from the surgical department at D4, plus or minus 1 day, to carry out lying-sitting and sitting-standing transfers, walk 30 metres and go up and down one flight of stairs;
- speed of postoperative functional recovery within the first 6 months (area under the curve of the function subscale of the WOMAC index).

### **II.2 - SECONDARY OBJECTIVES**

The secondary objectives in these patients with knee osteoarthritis for whom a TKA is scheduled are as follows:

1) Clinical assessment at 6 months and 12 months:

- a. participation (personalized WOMAC);
- b. pain (visual numeric scale 0-100);
- c. quality of life (SF-12);
- d. capacities - number of steps (pedometer);
- e. treatment satisfaction.

2) Health economics evaluation for the intervention. The costs of the two strategies will be compared at 6 and 12 months by taking into account the perspectives of the payer (Health Insurance) and the healthcare system. In addition, patients' quality of life will be estimated at the enrolment visit, and 6 months and 12 months after the procedure, using the EuroQoL questionnaire (EQ-5D) [Brooks 1996, Fransen 1999] (Annex 5). In the event that the most expensive strategy is the one that provides the best medical outcome and the best quality of life, we will carry out a cost-effectiveness analysis.

Implementing and evaluating complex intervention strategies such as combining educational and supervised exercise programmes is complicated and raises a number of specific methodological issues. Recently published recommendations [Craig 2008] highlight the need to take into account multiple endpoints. Indeed, complex interventions have multiple objectives (improving function, patient information and changing patient behaviour in terms of physical activity and weight-loss).

## **III - METHODOLOGY**

### **III.1 - STUDY TYPE**

This is a randomised, controlled, multi-centre, prospective study.

### **III.2 - STUDY DURATION**

The planned enrolment period is 21 months. The study is therefore expected to last 36 months. The patients taking part in the study will be monitored for between 14 and 15 months depending on the time elapsed between the enrolment visit and the intervention for the multidisciplinary programme.

The patients will not be able to take part in a biomedical research study with therapeutic assessment likely to change the primary and secondary endpoints of the EDEX study for a duration of 15 months.

Following the study, there is no exclusion period during which participation in another study is prohibited.

### **III.3 - EXPERIMENTAL DESIGN**

We are going to implement a randomised, controlled, multi-centre trial comparing:

- 1) usual treatment provided by the surgeon;
- 2) usual treatment provided by the surgeon combined with standardised and personalised multidisciplinary treatment.

The randomised, controlled trial is considered the gold standard for therapeutic assessment.

The study plan, its implementation, analysis and final write up of the results will be carried out in accordance with the CONSORT statement recommendations [Altman *et al.* 2001] and their extensions for non-pharmacological trials [Boutron, Ravaud *et al.* 2008], and the recommendations of the Medical Research Council for developing and evaluating complex interventions [Craig *et al.* 2008].

The patients randomised into the control group will not have any specific treatment apart from the standard treatment proposed by the surgeon and the messages from a knee arthroplasty guide. This choice allows patients to be in the situation which most accurately represents the current clinical practice and takes into account the lack of a standard treatment having proven to be effective which will be used according to consensus for all the sites.

This choice leads to some methodological issues, as blinding of patients, surgeons and the medical and paramedical team responsible for patient management will not be possible. As a result, there will be a risk of bias in performance and assessment. To take into account these risks, we will:

- a) Systematically collect the co-interventions prescribed in each group (analgesic treatments, physiotherapy prescription, number of consultations with the surgeon) to assess the risk of contamination and performance bias;
- b) Organise an independent assessment by a clinical study technician.

The patients will be informed that the aim of this study will be to compare two treatments for patients in the preoperative period, which are different and possibly effective. To this end, we will explain that they can have either routine care provided by their surgeons, or multidisciplinary care consisting of 4 exercise and therapeutic education sessions while awaiting the surgical intervention, in addition to the routine care.

### **III.4 - PATIENT ENROLMENT AND RANDOMISATION**

#### **Randomisation characteristics**

Randomisation will be stratified by site. The randomisation list will be prepared with variable block sizes. The list and block size will not be communicated to the investigators. The secrecy of the assignment will be maintained using an electronic randomisation system.

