### **4. Health economics evaluation**

This is a prospective study in which resource consumption by the patients in each arm will be collected in the case report form and evaluated 1) from the Health Insurance perspective, based on the reference nomenclature and prices in force at the end of the study, and 2) from the care-system perspective using the available hospital accounting data.

The resources collected include:

- time period before the intervention by the surgeons in the control group, and by the teams in charge of education and rehabilitation management in the intervention group;
- length of hospital stay and GHM (or the components of the medical unit summary) corresponding to the stay for the intervention;
- length of stay at rehabilitation care facilities;
- consultations and nursing or physiotherapy procedures during the follow-up period;
- imaging studies and medications consumed during follow-up;
- length of time off work or the time taken to resume normal activity.

There are, a priori, no structure costs related to the intervention as this uses existing capacities. However, we can consider designing a budgetary impact and an impact in terms of therapeutic education professionals if this intervention was to be widely used.

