### **4.4 Management of missing data**

In the event of missing data regarding the primary endpoints, multivariate imputation by chained equations (MICE) will be carried out.

Imputations will be carried out separately for the patients in the two groups. The baseline characteristics and the primary endpoints (ability at discharge and AUC of the function subscale of the WOMAC index) will be used in the prediction model. Predictive mean matching imputation will be used for the continuous data, logistic regression will be used for the binary data and multinomial regression will be used for the categorical data.

For the MICE procedure, it is common practice to use 10 iterations (Raghunathan TE, Solenberger PW, Van Hoewyk J. IVEware: Imputation and Variance Estimation Software. Ann Arbor, MI: Survey Methodology Program, Survey Research Center, Institute for Social Research, University of Michigan; 2007.

<http://www.isr.umich.edu/src/smp/ive/>). This value will therefore be used. For the number of imputations, it has been suggested as a general rule to use the same number of imputations as the percentage of observations with missing data (White IR *et al.*, Stat Med, 2010, 30: 377-399). This recommendation will be followed with rounding up to the next unit.

Convergence of the multiple imputation algorithm and the imputation results will be verified (van Buuren S & Groothuis-Oudshoorn K, J Stat Soft, 2011, 45: 1-97)

On the other hand, it has been demonstrated that using multiple imputation does not improve the results in mixed models for longitudinal data and that mixed models on imputed data can give unstable results (Twisk J *et al.*, J Clin Epidemiol, 2013, 66 :1022-1028). The secondary endpoints, analysed using longitudinal mixed models, will therefore not be imputed.

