#### **5.1.2 Primary analysis**

The proportion of patients who are independent at the time of discharge from the surgical department in each of the arms, the difference between these proportions and their ratio (rate ratio) will be estimated as well as their standard errors. The estimation of the difference in the rate of independence and the rate ratio will be adjusted to the centre. The adjusted analysis of the rate ratio will use a GEE Poisson model with an exchangeable correlation structure assuming a correlation for patients operated on by the same surgeon. The centre will be used as a fixed effect. The adjusted difference in proportions will be derived from the model used for the rate ratio. The analyses will be carried out on each of the imputed databases then pooled according to Rubin's Rules.

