### **5.2.2 Primary analysis**

The average area under the curve of the function subscale of the WOMAC index will be estimated in each of the groups. These averages will be compared using a linear mixed regression model with the randomisation arm and the centre (adjustment variable) as explanatory variables and the area under the curve of the function subscale of the WOMAC index as the response variable. The analysis will also be adjusted for the surgeon effect (random effect). The adjusted mean difference will be derived from this model. The analyses will be carried out on each of the imputed databases then pooled according to Rubin's Rules.

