#### **7.1.2 Analysis**

Adverse events and their characteristics will be described in the form of sample sizes and percentages by treatment arm. Fisher's exact tests will be used to compare the two treatment arms in terms of the proportion of patients with at least one AE/SAE and the proportion of patients with at least one SAE. The total number of AEs/SAEs and SAEs will also be described for each arm.

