## **8 Health economics analysis**

The EQ-5D scores will be converted into utilities based on French value tables. The utilities imputed for the periods corresponding to the interval between 2 collections will be multiplied by the corresponding durations to obtain QALYs. The differences in QALYs will be compared between the two groups.

The intervention will be valued on a flat-rate basis based on the time spent by the professionals as described in the protocol and by multiplying the estimated cost of each session by the proportion of patients having undergone the sessions.

Hospital admissions related to the pathology (imputed during the end-of-study meeting) will be valued based on 1) ENCC (French national hospital costs study database) costs and 2) rates. The costs will be estimated for each patient and the average costs in each arm will be compared using non-parametric tests.

The incremental cost-utility ratio will be calculated by comparing the difference in average costs with the difference in average QALYs, with a bootstrap sensitivity analysis.

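### Randomisation is stratified by site and every clinical efficacy model adjusts for centre, but the cost, QALY, bootstrap and adverse-event comparisons do not mention site; including it is a free gain in precision if site matters

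*Supplement*

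**What the plan says.** The latest protocol, III.4, reads: "Randomisation will be stratified by site". There are three sites, with variable block sizes.

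SAP v2.0 follows the design in its clinical efficacy analyses. In 5.1.2, for independence at discharge, "The centre will be used as a fixed effect". In 5.2.2 the WOMAC area under the curve is analysed by a "linear mixed regression model with the randomisation arm and the centre (adjustment variable) as explanatory variables". The models in 6.1 to 6.5 all list centre as an adjustment variable.

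Three other parts of the SAP do not mention site or centre:

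- **SAP 8, costs:** "the average costs in each arm will be compared using non-parametric tests".
- **SAP 8, QALYs:** "The differences in QALYs will be compared between the two groups". No test, model or covariate is named. A bootstrap is attached to the cost-utility ratio, and protocol IX.4 (item 4) refers to bootstrap confidence intervals; neither gives a resampling scheme.
- **SAP 7.1.2, adverse events:** Fisher's "exact tests will be used to compare the two treatment arms". No interval is planned.

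SAP 4.4 describes the imputation model for the primary endpoints: "The baseline characteristics and the primary endpoints (ability at discharge and AUC of the function subscale of the WOMAC index) will be used". The baseline characteristics are not listed, so centre is neither named nor excluded.

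**The concern.** When allocation is balanced within site, differences between sites largely cancel out of the arm comparison. A pooled standard error still counts them. If site predicts the outcome, the pooled analysis therefore overstates the uncertainty: its intervals are too wide, and its tests run below their nominal level and lose power. A bootstrap that resamples only within arm has the same fault, because it recreates site imbalances that the randomisation limited.

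There are qualitative grounds to expect some site effect on resource use. Control patients receive whatever information and advice is customary at their centre (protocol I.2 and VII.2). The programme runs in rehabilitation departments at two sites and a rheumatology department at the third. The resources counted include acute stay, rehabilitation stay and physiotherapy, which may follow local discharge practice. At stake are the precision of the economic results and their consistency with the clinical results in the same report.

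**Working it through.** **Figures in the plan.** The documents state no sample size, power or variance for the cost, QALY or adverse-event comparisons. Protocol IX.2 justifies the sample size on the two primary endpoints only, so there is no planned figure to reproduce here.

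**Inputs.**
- 150 patients per arm (protocol IV.3).
- Site mix from protocol IV.5: 280 × 70% × 30% = 58.8, 200 × 90% × 30% = 54 and 200 × 70% × 30% = 42 per year. Scaled to 150 per arm, this is 57, 52 and 41.
- Two-sided 5% level. This is assumed: SAP 4.1 gives 5% for secondary endpoints and does not name the economic or adverse-event tests.
- Share of outcome variance explained by site, R²: not in the documents, varied from 0 to 0.20.
- True difference for power: 0.33 within-site standard deviations, chosen to give about 80% power. It is not a figure from the plan.

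**Formula.** With total variance σ² and n per arm balanced within site, the pooled standard error is √(2σ²/n), and the one the design warrants is √(2σ²(1 − R²)/n). The ratio is 1/√(1 − R²). For R² = 0.10 this is 1/√0.90 = 1.054.

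**Simulation.** Normal outcomes, 4,000 trials per setting for the tests. The bootstrap column averages 60 data sets of 600 resamples each. The last four columns are percentages; MW is Mann-Whitney (pooled) and vE is van Elteren (site-stratified).

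| R² | SE ratio, formula | SE ratio, simulated | Bootstrap width ratio | MW level | vE level | MW power | vE power |
|---|---|---|---|---|---|---|---|
| 0 | 1.000 | 1.000 | not run | 5.1 | 5.2 | 78.9 | 78.7 |
| 0.01 | 1.005 | 1.005 | not run | 4.9 | 5.0 | 79.4 | 79.7 |
| 0.05 | 1.026 | 1.026 | 1.032 | 4.3 | 4.9 | 78.0 | 79.0 |
| 0.10 | 1.054 | 1.055 | 1.059 | 3.8 | 4.8 | 75.0 | 78.1 |
| 0.20 | 1.118 | 1.119 | 1.134 | 3.1 | 5.4 | 71.9 | 79.2 |

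The power lost by the pooled rank test is 1.0, 3.1 and 7.3 points at R² = 0.05, 0.10 and 0.20. For means, a t-test against a linear model with site gives 80.0 v 81.2%, 77.5 v 80.8% and 74.2 v 81.3%, a loss of 1.2, 3.3 and 7.1 points. The Monte Carlo standard error of each power figure is about √(0.79 × 0.21/4000) = 0.6 points. Both tests were run on the same data sets, so the differences are more precise than that.

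**Adverse events.** 3,000 trials per setting, with a 14-point true difference.

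| Site rates | Fisher | Chi-squared | Site-stratified Mantel-Haenszel |
|---|---|---|---|
| 20/20/20% | 74.8% | 78.1% | 78.0% |
| 10/20/30% | 76.1% | 79.6% | 80.3% |
| 5/20/40% | 75.4% | 79.5% | 82.6% |

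With rates of 10/20/30%, Fisher falls 80.3 − 76.1 = 4.2 points short, of which 79.6 − 76.1 = 3.5 come from Fisher's own conservatism and 0.7 from leaving out site. With 5/20/40% the split is 4.1 and 3.1 of 7.2 points.

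**The case against.** The strongest reply is that the harm is conditional on a site effect that nothing in the documents quantifies. At R² of 1% or less the loss is negligible. SAP 8 also narrows the room for a large effect. It values the intervention at a flat rate and admissions at national reference costs or tariffs, so site price differences largely drop out. Protocol IX.4 does plan one perspective "from the care-system perspective using the available hospital accounting data", but its base calculation is the Health Insurance perspective, where admissions are priced by tariff and earlier discharge is described as cost-neutral.

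This stands as a limit on size. It does not remove the point, because uniform prices leave differences in resource use between sites untouched.

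A reader might also infer that SAP 8 prescribes a bootstrap on pooled arms and an unadjusted QALY test. The text does not say so: it is silent on both. Nor can adverse-event intervals be called too wide, since none is planned, and most of Fisher's power shortfall has nothing to do with site.

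On imputation, the unlisted baseline characteristics in SAP 4.4 may already include centre. No effect of its omission has been quantified.

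**Conclusion.** The inconsistency is real in the latest documents. The design factor enters every clinical efficacy model but is not mentioned in the cost, QALY, bootstrap or adverse-event comparisons, and no reason is given.

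The consequence is modest and in the conservative direction. If site explains 5%, 10% or 20% of the variance, mean-difference and bootstrap intervals would be about 3%, 6% and 12–13% too wide, with about 1, 3 and 7 points of power lost; at R² = 0 nothing is lost. These figures rest on an assumed R², close balance within site, normal outcomes and an effect size chosen for illustration.

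One might be tempted to say outright that the intervals are too wide and that the trial loses power. The documents support neither statement: the site effect is unknown, and the trial was never powered on these comparisons. Leaving out site does not inflate false positives here. This is a gain in efficiency and consistency, not an error that threatens a conclusion.

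**What to change.** **SAP 8, the main change.** Estimate the mean cost and mean QALY differences with site as a covariate, or use a site-stratified rank test such as van Elteren for costs. State that bootstrap samples are drawn within each site-by-arm cell. Name the method for the QALY comparison.

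**Minor additions.** In SAP 7.1.2, use a site-stratified test, for example an exact Cochran-Mantel-Haenszel test. In SAP 4.4, name centre among the imputation predictors, so that the imputation model visibly contains what both primary models contain.

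**Cost.** A few words in three sections. Site is known for every patient, so no new data are needed. Three sites use two degrees of freedom. When site had no effect, stratifying cost essentially nothing in the simulation (78.7% against 78.9% power).

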#### **Enrolment and randomisation procedure**

Taking into account the lack of availability of clinicians, and surgeons in particular, patient enrolment in clinical trials is difficult. To compensate for this difficulty, patient screening will be carried out by a clinical study technician.

The clinical study technician will systematically identify all patients who have been scheduled to undergo knee arthroplasty. As agreed with the surgeon in charge of the patient, the clinical study technician will contact the potentially eligible patient and will propose that he or she participate in the EDEX study. If the patient is interested in this study, a consultation will be scheduled, which must take place on the same day as the pre-anaesthesia consultation. During this consultation, the rehabilitation physician or the rheumatologist, assisted by the clinical study technician, will confirm the eligibility criteria, will give the patient the relevant information and, after obtaining the patient's consent, the patient will be randomised. Patients randomised into the intervention group will be contacted by the clinical study technician to arrange for the intervention to be carried out.

## **IV - STUDY POPULATION**

### **IV.1 - INCLUSION CRITERIA**

- Men or women aged from 50 to 85 years;
- Patients with knee osteoarthritis according to the ACR criteria for which total knee arthroplasty has been scheduled by the surgeon;
- Medical examination carried out in advance, the results of which will be communicated to the patient;
- Patients having provided their written informed consent to take part in the study;
- Patients affiliated with a social security scheme (beneficiary or entitled party).

